### Data sources

Patient-level TB data will be sourced from existing programmatic Ministry of Health facility registries and patient-level forms. Slight modifications may need to be designed to capture the entire TB care cascade from screening to TB-free survival. Data will be abstracted from these existing paper registries and patient forms at least weekly by study personnel into a study database via REDCap on tablet or laptop [53]. As part of routine care, each patient with TB is assigned a unique identification number that links across service points and clinics, which will be used to abstract registry data for study outcome measures. The database will generate on-demand reports with monthly indicators to populate the TCAT.

### Power and sample size

Power calculations are based on the primary outcome: mean change in proportion of individuals who complete screening for TB. TB screening was selected as the primary outcome as existing South African guidelines call for TB screening to be routinely implemented in outpatient services, and it is where the largest gap in the TB care cascade is currently. In a stepped wedge study, exposed and unexposed observation periods take the place of “arms” in parallel cluster trials. Outcomes (TB screening, TPT initiation, and TB treatment initiation) at baseline have been estimated to be 39% of eligible individuals screened for TB, 31% eligible individuals initiating TPT, and 70% eligible individuals initiating TB treatment per preliminary and national data (unexposed) [5, 23, 25]. We need a sample size of 978 individuals screened per cluster per time period to have 99% power (alpha = 0.05, and intracluster correlation of 0.01) to detect down to a 5% difference of proportion. Therefore, each cluster, over the course of all 5 time periods, needs to screen 4890 individuals. With four clusters, that will produce a total sample size of 19,560. Power calculations were completed using the Pass power analysis and sample size statistical software [54].

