**Methods:**

This stepped-wedge cluster randomized trial will evaluate the effectiveness of SAIA on TB (SAIA-TB) cascade optimization for patients with TB and high-risk contacts across 16 clinics in four local municipalities in the Sarah Baartman district, Eastern Cape, South Africa. We hypothesize that SAIA-TB implementation will lead to a 20% increase in each of: TB screening, TB preventive treatment initiation, and TB disease treatment initiation during the 18-month intervention period. Focus group discussions and key informant interviews with clinic staff will also be conducted to determine drivers of implementation variability across clinics.

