### Outcomes

We will measure each indicator across the TB care cascade from TB screening to TB-free survival. (Table 2). Primary outcomes include the mean change in proportion of individuals (1) screened for TB disease, (2) initiated on TPT, or (3) initiated on TB disease treatment combined across all facilities during the intervention period (exposed) compared to baseline (unexposed). Primary outcomes were selected based on sensitivity to system-level improvements; they represent SAIA-TB steps that, if changed, would meaningfully alter patterns of TB-related morbidity and they are routinely collected. They are relatively easy to collect and readily understood by clinic managers and frontline staff. Indicators will be assessed monthly over the study period (including 12 months baseline, 18 months intervention, and 12 months maintenance phase).

**Table 2 Tab2:** SAIA-TB primary and secondary outcomes

SAIA-TB primary and secondary outcome variables	
**TB indicator (variable)**	**Numerator/denominator**
TB screening^a^	*#screened with WHO symptom screen* # target population
TB evaluation	*# receiving a diagnostic evaluation (GXP/LAM)* # positive screening
TB diagnosis	*# diagnosed with TB (GXP/LAM/clinical)* # who completed a diagnostic evaluation
Linkage to care for TPT^a^	*# initiating TPT* # negative diagnostic evaluation + eligible for TPT
Linkage to care for TB disease^a^	*# initiating TB treatment* # positive diagnostic evaluation
Successful TPT outcome	*# completing TPT* # initiating TPT
Successful TB outcome^b^	*# cure or complete treatment for TB disease* # initiating TB treatment
TB-free survival	*# TB-free (CXR/GXP) 12 months* *after initiating TPT or TB disease treatment* # successful outcomes for TPT or TB disease

*CXR* Chest x-ray, *GXP* GeneXpert, *LAM,* Urine lipoarabinomannan

^a^Primary outcome variable

^b^WHO definition

Secondary outcomes include the additional TB cascade indicators (TB evaluation, diagnosis, treatment outcome, and TB-free survival); however, some of these are more dependent on a mix of individual-level factors (i.e., adherence to medication) (Table 2). These indicators are clinically important and can be affected at a system-level. Outcomes will be assessed for all patients receiving care, as well as assessed by important sub-groups, such as by HIV status, age (under 5 years), and local municipality (cluster).

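### The power section names TB screening as the one primary outcome, while the Outcomes section and Table 2 name three, so the success criterion is contradictory and the stated power covers only one of them

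*Protocol article*

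**What the plan says.** The Power and sample size section uses the singular twice. It says "Power calculations are based on the primary outcome: mean change in proportion of individuals who complete screening for TB", and it justifies the choice: "TB screening was selected as the primary outcome as existing South African guidelines call for TB screening to be routinely implemented in outpatient services". It then lists baseline values for screening (39%), TPT initiation (31%) and TB-treatment initiation (70%), but sizes the trial for screening alone: 978 people screened per cluster per period, 99% power, a 5% difference, "alpha = 0.05, and intracluster correlation of 0.01".

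The Outcomes section uses the plural and lists three: "the mean change in proportion of individuals (1) screened for TB disease, (2) initiated on TPT, or (3) initiated on TB disease treatment". The Table 2 footnote marks the same three indicators as primary, and the Data analysis section also speaks of primary outcomes in the plural. The Methods paragraph of the abstract hypothesises that the strategy "will lead to a 20% increase in each of: TB screening, TB preventive treatment initiation, and TB disease treatment initiation".

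**The concern.** Three readings are open: screening is the only primary outcome, success on any of the three is enough, or all three must succeed. They have different false-positive rates and different power, and they can give opposite verdicts on the same data. The analysis plan is not shown and may hold a multiplicity rule, so the absence of such a rule here is not the point. The point is that the article disagrees with itself about what is primary, and the correct rule depends on the answer. The single power statement also sits in a section that lists baselines for all three outcomes, so its sensitivity could be credited to outcomes for which it was not calculated.

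**Working it through.** **1. The stated figure.** Inputs from the Power and sample size section: 4 clusters, 5 periods, 978 per cluster-period, ICC 0.01, alpha 0.05 (two-sided assumed), 39% against 44%. Model: cross-sectional stepped wedge with fixed period effects, a random cluster intercept and a normal approximation (Hussey-Hughes).

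Var = I·s²(s² + T·τ²) / [(I·U − W)s² + (U² + I·T·U − T·W − I·V)τ²], with s² = p(1−p)/m and τ² = p(1−p)·ICC/(1−ICC). One cluster crosses over per step, so I = 4, T = 5, U = 10, W = 30, V = 30, and the denominator is 10s² + 30τ².

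- p(1−p) = 0.39 × 0.61 = 0.2379; s² = 0.2379/978 = 0.000243; τ² = 0.2379/99 = 0.002403.
- SE = 0.01265; 0.05/0.01265 = 3.95; power = Φ(3.95 − 1.96) = 97.7%.

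That is close to the stated 99%. Exactly 99% needs 1,153 two-sided or 988 one-sided. The totals are exact: 978 × 5 = 4,890 and 4,890 × 4 = 19,560. The stated design therefore reproduces, for screening.

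**2. Error rate under each reading.**
- Screening only: 5%.
- Any of three at 5% each: 1 − 0.95³ = 14.3% if independent, less if positively correlated.
- All three: no inflation, but joint power cannot exceed the lowest of the three powers, and two are not stated.
- Any of three with Bonferroni, 0.05/3 = 0.0167: screening power at 978 is Φ(3.95 − 2.39) = 94%.

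**3. TB-treatment initiation.** Its Table 2 denominator is people with a "positive diagnostic evaluation". Inputs: 1,022 per 100,000 (Study setting, taken as annual and equal in each municipality), the Table 1 populations, and 3-month waves (Intervention phase). Cases per cluster per 3 months = population × 0.01022 / 4, counting every case in the municipality:

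| Municipality | Population | Cases per 3 months |
|---|---|---|
| Ndlambe | 69,130 | 177 |
| Sundays River Valley | 62,306 | 159 |
| Kouga | 120,273 | 307 |
| Kou-Kamma | 48,424 | 124 |

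The same model with these unequal counts, the average of the two binomial variances, and the mean over all wave orders gives:

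| Share of cases seen | Power, 70% to 75% | Power, 70% to 84% (20% relative) |
|---|---|---|
| All | 48% | over 99% |
| Half | 28% | 98.7% |
| A quarter | 17% | 86% |

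With all cases, for example, SE = 0.0261 and 0.05/0.0261 = 1.92, so power = Φ(1.92 − 1.96) = 48%. A 20-point increase, 70% to 90%, gives more power still.

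**4. Period length.** The article does not define its periods. For 99% power at 70% to 75%, treatment initiation would need 961 per cluster-period, or 961 × 5 = 4,805 per cluster. Over 39 months (12 baseline + 9 rollout + 18 intervention) the four clusters supply 1,608 to 3,995 cases each, about 9,970 in all. Split into five equal periods, that averages 9,970/20 = 498, between the 404 needed for 80% and the 545 needed for 90%. So 48% belongs to 3-month periods, and longer periods raise it, but 99% stays out of reach.

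**5. TPT initiation.** The article gives no count for its denominator, so the sizes below are assumptions:

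| Per cluster-period | 31% to 36% | 31% to 37.2% (20% relative) | 31% to 51% (20 points) |
|---|---|---|---|
| 200 | 47% | 65% | over 99% |
| 400 | 75% | 90% | over 99% |

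**The case against.** The strongest reply is that the power section says openly that its calculation rests on screening, and that 978 counts people screened. No sentence applies 978, 4,890 or 99% to treatment initiation. This stands. A reader might infer that the trial requires 978 treatment-eligible people per cluster-period and cannot find them; the article makes no such requirement.

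A second reply is that 5 points is the difference used for screening, while the effect hypothesised for each outcome is a 20% increase. This also stands. It defeats the inference that the trial is underpowered on all outcomes other than screening: for treatment initiation, power is adequate for the hypothesised effect on either reading of 20%. For TPT the answer depends on the reading of 20% and on a denominator that the article does not give.

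A third reply is that multiplicity handling may sit in the full protocol or analysis plan, that the word joining the three outcomes only lists them, and that the abstract's hypothesis about all three points away from an any-of-three rule. This is fair, and 14.3% is accordingly conditional. It does not remove the conflict, because the power section says which single outcome was chosen and why, and the Outcomes section and Table 2 say otherwise.

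**Conclusion.** The article is wrong as written on one point: it names one primary outcome where it sizes the trial and three where it defines outcomes. The consequence is an undefined success criterion. The family-wise error is up to 14.3% if any one outcome suffices and the tests are independent; if all must succeed, two of the three have no stated power.

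The 99% power at 5 points belongs to screening. Treatment initiation has about 48% at 5 points, assuming annual incidence, 3-month periods and all cases seen. It has about 86% to over 99% for a relative increase to 84%, with a quarter to all of the cases seen. All these powers assume a constant within-cluster correlation and a normal approximation with four clusters, and are therefore optimistic: at a cluster autocorrelation of 0.9, screening power at 978 falls to about 81%.

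**What to change.** Reconcile the abstract, Outcomes section, Table 2 footnote, Power and sample size section and Data analysis section. The simplest way is to make TB screening the single primary outcome throughout, since the power section already justifies it. TPT and then TB-treatment initiation become key secondary outcomes, tested in that fixed order at 5% after screening succeeds.

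If three primary outcomes are kept, state whether any or all must succeed and set alpha to match. An any-of-three rule at 0.0167 leaves screening about 94% power at 978. An all-must-succeed rule needs no split but needs a power statement for each outcome and for all jointly.

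In either case, say whether the 20% increase is relative or absolute, and give the detectable difference for TPT and treatment initiation at their expected denominators, with a range.

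The cost is wording in the protocol, the analysis plan and, where affected, the registry entry; design and data collection do not change. The downside of a single primary outcome is that a TPT or treatment effect is not confirmatory if screening fails.

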### Data analysis

Intervention analysis for primary outcomes will include generalized linear mixed modeling comparing study outcomes between exposed and unexposed times for outcomes described in Table 2 [31, 55]. Models will account for clustering by local municipality and will assess the impact of adjustment for patient-level covariates (i.e., age, sex, HIV status, and comorbidities) as well as clinic-level covariates (i.e., patient volume, staffing levels) and time (months since study initiation). We will assess missing data for randomness and employ multiple imputation, if possible [56, 57]. Additionally, we will assess outcomes among all individuals, including patients lost to follow-up, following an intent-to-treat principle [58–60]. Secondary analyses will test for interaction between exposure and time (temporal and time-to-exposure) to avoid a bias estimate of treatment effect [31]. We will also conduct a controlled, segmented time-series analysis incorporating monthly clinic-level estimates from the entire study period (segmented into 12-month baseline, 18-month intervention, and 12-month maintenance phases). This secondary analysis will allow us to fully use available data to assess intervention impact, address both serial and intra-class correlation, and assess temporal patterns in study outcomes [55, 58].

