### SAIA-TB trial design

This study is a 5-year, four-wave stepped wedge cluster randomized trial design to assess the effectiveness of the SAIA-TB strategy (Fig. 1; Consort Checklist, Additional file 1). Each wave includes four local municipalities within a district, with four health facilities per local municipality purposively selected to receive SAIA for a total of 16 facilities. Each local municipality represents a cluster and will be randomized for intervention wave. Each facility will have at least 12 months of baseline data collection followed by 18 months of intervention and 12 months of a measured maintenance phase (Fig. 3).

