#### Intervention phase

Clusters will begin the *intervention phase* in waves, starting every 3 months. Each cluster will receive a 3- to 4-day orientation from the study team and district health authorities on SAIA-TB components. Orientation will include practice with populating and interpreting the TCAT, developing process maps of current TB and TPT patient care pathways for screening, evaluation, diagnosis, and management, and engagement in their first CQI meeting whereby they identify, prioritize, and define their first micro intervention. Subsequently, district TB supervisors, together with study personnel, introduce SAIA-TB to intervention health facilities over a 2-day period. Within each local municipality, SAIA-TB is introduced to all facilities together, and then independent facility visits will be conducted. Facility teams receive bi-weekly supervision visits by study personnel and district supervisors for the first month, followed by monthly visits throughout the remainder of the 18-month intervention phase, consistent with most adaptations of SAIA globally.

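### The primary model names municipality as its only clustering level and has no term for drift between periods, so the standard error for TB screening is too small if municipalities or clinics drift

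*Protocol article*

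**What the plan says.** The primary analysis is "generalized linear mixed modeling comparing study outcomes between exposed and unexposed times" (Data analysis). On correlation the same section says "Models will account for clustering by local municipality". Clinics enter through covariates such as volume and staffing. Months since study start stands in the same list of terms whose adjustment will be assessed.

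Under SAIA-TB trial design, "Each local municipality represents a cluster and will be randomized for intervention wave", "with four health facilities per local municipality purposively selected to receive SAIA for a total of 16 facilities". Under Intervention phase, "Clusters will begin the *intervention phase* in waves, starting every 3 months".

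Tests for interaction between exposure and time, and a segmented time-series analysis of monthly clinic-level estimates meant to "address both serial and intra-class correlation", are both labelled secondary. The Power and sample size section uses one "intracluster correlation of 0.01" and mentions no decay over time.

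**The concern.** A model with municipality as its only random term treats all remaining variation, given municipality and time, as patient-level noise. That is right only if a municipality's screening level never moves between periods apart from the trend shared by all four.

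The protocol describes a setting in which levels are likely to move: each clinic picks its own workflow changes in repeated cycles, and structural readiness is reassessed before each phase because it may change. Variation of this kind does not shrink as more patients are recorded, whereas the model's standard error does. A shift in one municipality near its crossover date could then be read as an intervention effect. What is at stake is the p-value and confidence interval for TB screening, the outcome on which the trial is powered.

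**Working it through.** **Inputs from the protocol.** Four clusters, five periods, 978 per cluster-period, ICC 0.01, alpha 0.05 (taken as two-sided), baseline screening 39%, difference 5 points (Power and sample size); four clinics per municipality (SAIA-TB trial design). Outcome variance s = 0.39 × 0.61 = 0.2379.

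**Assumptions.** The CAC, meaning the share of cluster variance that is stable between periods, is not in the document and is varied from 1.0 to 0.8. The split of cluster variance between municipality and clinic is also unknown, so both extremes are shown. Period is fitted as a full categorical term, which favours the plan because time adjustment is only to be assessed.

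**The plan's own figure.** The standard stepped-wedge variance with one constant cluster intercept gives SE = 0.0126. Power = Φ(0.05/0.0126 − 1.96) = Φ(2.01) ≈ 97.8% (97.5–98.1% over variants of the variance), against the stated 99%. The sizes agree: 978 × 5 = 4,890 and 4,890 × 4 = 19,560. The stated power is thus close to what a calculation without drift gives.

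**Type I error of the municipality-only model.** The true variance adds a cluster-by-period component ICC × (1 − CAC) × s. The true SE of the municipality-only estimator comes from the sandwich formula, and type I error = 2[1 − Φ(1.96 × model SE / true SE)].

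| CAC | All variance at municipality level: model SE, true SE, error | All variance at clinic level: model SE, true SE, error |
|---|---|---|
| 1.0 | 0.0126, 0.0126, 5.0% | 0.0124, 0.0124, 5.0% |
| 0.95 | 0.0126, 0.0153, 10.8% | 0.0124, 0.0131, 6.4% |
| 0.9 | 0.0126, 0.0177, 16.3% | 0.0123, 0.0137, 7.8% |
| 0.8 | 0.0126, 0.0216, 25.3% | 0.0123, 0.0149, 10.6% |

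**Hand check.** With all variance at municipality level, the SE ratio is roughly √[1 + ICC(1 − CAC)n/(1 − ICC)]. At CAC 0.8 this is √[1 + 0.01 × 0.2 × 978/0.99] = 1.73, against 0.0216/0.0126 ≈ 1.72 above.

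**Simulation on binomial data (1,000 runs per setting, linear mixed and logistic models).** Type I error was 5–7% at CAC 1, including when all variance was a stable clinic effect. With all variance at municipality level it was 18–19% at CAC 0.9 and 27% at CAC 0.8. With half at clinic level it was 21% at CAC 0.8.

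**How much drift this is.** The between-period SD of a municipality's level is √[0.01 × (1 − CAC) × 0.2379]: 1.1 percentage points at CAC 0.95 and 2.2 points at CAC 0.8.

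**Smaller denominators.** At an assumed 100 per cluster-period and CAC 0.8, the hand formula gives √[1 + 0.01 × 0.2 × 100/0.99] = 1.10 and an error of about 7%. With all variance at clinic level the error is between 5% and 6%.

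**Few clusters.** With a municipality-by-period effect, 20 cluster-periods minus 9 parameters (4 municipality, 4 period, 1 exposure) leave 11 df. Using z instead of t on 11 df gives P(|t| > 1.96) ≈ 7.6%.

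**Power at CAC 0.8, all variance at municipality level.** Φ(0.05/0.0216 − 1.96) ≈ 64% by z, or about 56% with t on 11 df.

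**The case against.** The strongest reply has four parts.

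- **The inflation rests on a CAC that the protocol does not give.** This stands: at CAC 1 there is none. A reader might infer that type I error is far above 5% as a matter of fact. The document does not support that, and only a range can be given.
- **Clustering at the randomised level is right.** This also stands. A reader might infer that leaving out clinics is the fault. All clinics in a municipality cross over together and are observed in every period, so omitting a stable clinic intercept leaves the error at 5.0–5.1%, even with unequal clinic sizes. Only variation between periods, at clinic or municipality level, does harm.
- **Time and serial correlation are not ignored.** Time is a candidate adjustment, and the secondary analyses address interaction and serial correlation. This is correct, but a common time trend does not absorb drift specific to one municipality, and a secondary analysis does not protect the primary p-value.
- **A condensed article may leave random-effects detail and small-sample methods to the analysis plan.** A missing small-sample method alone would not be a finding. But the article does state a clustering level for the primary model and does assign serial correlation elsewhere, so the choice is stated.

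**Conclusion.** The point holds in conditional form. As written, the primary model has no term for municipality-by-period or clinic-by-period variation. If such variation exists, the standard error for TB screening is too small. At the planned size, type I error is about 6–11% at CAC 0.95 and 11–25% at CAC 0.8. These figures assume ICC 0.01, five periods and 978 per cluster-period.

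Two wider readings are not supported.

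- **Every primary outcome is affected to the same degree.** The calculation is for screening. TPT and TB treatment initiation have narrower denominators whose sizes are not given, and at an assumed 100 per cluster-period the error is only about 5–7% at CAC 0.8.
- **The error reaches 54%.** That needs 4,500 people per cluster-quarter, which reads the 4,500 outpatient visits in Eligibility criteria as per clinic. The text gives that figure among the reasons for choosing municipalities. Read so, it is 4,500/4 = 1,125 visits per quarter, close to 978, and the range at CAC 0.8 is 11–28%. It is also a minimum and counts visits, not people. What remains true is that the inflation grows with cluster-period size.

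**What to change.** In the primary model:

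- make calendar period a mandatory term;
- add a municipality-by-period random effect or a decaying within-cluster correlation, plus clinic and clinic-by-period effects where estimable;
- use few-cluster inference, for example a t reference with cluster-period degrees of freedom (11 in the five-period layout).

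Report the permutation p-value over the 4! = 24 wave orders as a check only. Its minimum is 1/24 = 0.042, reached only if the realised order is the single most extreme.

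With four municipalities this reduces the problem but may not remove it. In a smaller set of simulations at CAC 0.8 with all variance at municipality level, adding the municipality-by-period effect and t on 11 df brought the error from about 27% to about 10%. With half the variance at clinic level it fell from about 21% to about 7%.

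The cost is analysis wording, wider intervals, and a power statement that must be restated over a range of CAC: at CAC 0.8 with all variance at municipality level, power is about 64% by z, not 99%.

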## Discussion

At the completion of this pragmatic stepped wedge cluster randomized trial, important knowledge regarding the effectiveness of SAIA-TB on TB cascade optimization for patients with TB and high-risk contacts, specifically PLH in a high burden TB/HIV context will be gained. Drivers of SAIA-TB implementation variability across clinics and fidelity to the intervention will be better understood, providing robust evidence for translation, scale-up, and dissemination. Given the rapidly evolving landscape of TB guideline development on the global and national level, this intervention provides opportunity to be at the forefront of implementing newly released TPT regimens as they become available within the public sector. Our agility within the SAIA strategy provides clinics opportunity for knowledge sharing and innovation as we take lessons learned from the pandemic and translate and harness them for TB and HIV services [72, 73]. Finally, adaptations from previous SAIA iterations will be documented to aid in future SAIA implementation in additional health conditions and across geographically diverse settings.

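### The plan does not commit to a time-adjusted primary estimate, although exposure is confounded with calendar time in a stepped wedge

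*Protocol article*

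**What the plan says.** The Outcomes section defines the primary outcomes as mean changes in proportions, "combined across all facilities during the intervention period (exposed) compared to baseline (unexposed"). It does not mention calendar time in that definition.

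The Data analysis section specifies generalized linear mixed models "comparing study outcomes between exposed and unexposed times for outcomes described in Table 2". Its next sentence uses two verbs of different strength: "Models will account for clustering by local municipality and will assess the impact of adjustment for patient-level covariates". The list that follows continues "as well as clinic-level covariates (i.e., patient volume, staffing levels) and time (months since study initiation"). Clustering is thus a commitment. Time stands in the same list as age, sex and staffing, as something whose adjustment will be examined. The section does not say which of the resulting models is primary or in what form time enters.

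Secondary analyses are an interaction between exposure and time (calendar time and time to exposure) and a segmented time series "segmented into 12-month baseline, 18-month intervention, and 12-month maintenance phases".

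On the length of baseline, the SAIA-TB trial design section and the section on pre-implementation and baseline data collection give 12 months as a minimum. The Exposure definition counts a facility as unexposed until the intervention starts in its own municipality. The Outcomes section and the segmented analysis give 12 months flat.

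**The concern.** All four municipalities move in one direction, from unexposed to exposed, so exposed months are later months. What separates the intervention from the calendar is the randomised order of the waves, and an analysis uses that order only if it compares clusters within calendar periods. A pooled exposed-versus-unexposed contrast without a time term is a before-after comparison. Calendar time is therefore part of the design in a way that sex or staffing level is not, and whether it is in the primary model should not be left open.

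Drift is plausible here on the protocol's own account. The Background reports that eligibility for preventive treatment was widened in late 2021, and the Discussion places the trial in this context: "Given the rapidly evolving landscape of TB guideline development on the global and national level". A national change in screening or preventive treatment during the trial would move the same proportions that SAIA-TB is meant to move. If the time-free estimate were the one reported, that change would be credited to SAIA-TB.

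**Working it through.** **Inputs.** From the Power and sample size section: 4 clusters, 5 periods, 978 per cluster-period, ICC 0.01, alpha 0.05, baseline screening 39%, difference 5 points, power 99%. From the trial design and Intervention phase sections: at least 12 months of baseline, waves every 3 months, 18 months of intervention. Assumed: two-sided alpha; starts after 12, 15, 18 and 21 months; 978/3 = 326 people per cluster-month; all trend sizes.

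**The plan's own figures.** 978 × 5 = 4890 and 4890 × 4 = 19,560, as stated. For power with period effects in the model, the Hussey-Hughes variance is

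Var = Iσ²(σ² + Tτ²) / [(IU − W)σ² + (U² + ITU − TW − IV)τ²]

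with I = 4, T = 5, U = 10, W = 30, V = 30. So IU − W = 10 and U² + ITU − TW − IV = 100 + 200 − 150 − 120 = 30. Here σ² = 0.39 × 0.61/978 = 0.000243 and τ² = (0.01/0.99) × 0.2379 = 0.00240. This gives SE = 0.01265 and power Φ(0.05/0.01265 − 1.96) = 97.7%, within 2 points of the stated 99%. Without any time term the SE is 0.00778 and power exceeds 99.9%. The ratio of SEs is 0.01265/0.00778 = 1.63.

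**Distance in calendar time.** Numbering months from 0, the waves contribute 12 + 15 + 18 + 21 = 66 unexposed cluster-months with mean month 534/66 = 8.09, and 72 exposed cluster-months with mean month 25. The gap is 16.9 months.

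**Bias with no time term, true effect zero.**
- Pooled contrast: a rise of 5 points per year gives 16.9 × 5/12 = 7.0 points. A spurious 5 points needs 5 × 12/16.9 = 3.5 points per year.
- Mixed model with a random cluster intercept: 0.1, 0.2 and 0.3 points per month give 1.7, 3.5 and 5.2 points.
- 5-period planning layout: a rise of 0.5, 1 or 2 points per 3-month step gives 1.2, 2.5 or 5.0 points.

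**Bias with time in the model, monthly timeline, true effect zero.** A linear months term removes any linear trend exactly. For a one-off 5-point shift common to all clusters:

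| Month of shift | No time term | Linear months | Categorical periods |
|---|---|---|---|
| 6 | +1.9 | -1.0 | 0 |
| 12 | +3.7 | +1.4 | 0 |
| 15 | +4.2 | +2.2 | 0 |
| 18 | +4.2 | +2.1 | 0 |
| 24 | +3.0 | -0.4 | 0 |
| 30 | +1.4 | -1.2 | 0 |

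The last column is the same for monthly and 3-month categories. In the symmetric 5-period layout the linear term also leaves no bias; the residual arises on the longer planned timeline. The SEs on that timeline are 0.46, 0.90 and 1.10 points for the three models.

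**Concurrent comparison.** Unexposed months that run beside an exposed cluster number 3 + 6 + 9 = 18. They are exactly the months of waves 2 to 4 beyond month 12.

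**A limit of the time-adjusted model.** If the effect grows linearly to 10 points over 18 months, its mean over exposure is 5.3 points. A constant-effect model with cluster and month effects returns 0.4.

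**The case against.** The strongest reply is that time is a named term for these models. A reader might infer that any secular trend will be read as a SAIA-TB effect. The document does not support that: once months are entered, even linearly, the 7-point illustration falls to 0. The stated sample size also sits nearer the time-adjusted model: 99% power for 39% to 44% needs 1153 to 1174 per cluster-period with time and only 433 to 441 without. This stands, and it limits the point to a missing commitment.

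A reader might also infer that the unexposed months of later waves beyond month 12 are discarded. The trial design section, the baseline data collection section and the Exposure definition say otherwise, and the primary model compares exposed with unexposed times. What remains is loose wording in the Outcomes section and in the segmented analysis.

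It can be said that the functional form of time belongs in a fuller document. In general that is fair. Here the article itself states the role of time, and states it as optional. Since the sentence has to be corrected anyway, the form should be settled with it.

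Finally, the remedy has its own weakness, shown by the growing-effect example, and the protocol already plans a time-to-exposure analysis. That is correct. It argues for reporting that analysis beside the primary one, and it does not justify leaving time out of the primary model.

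**Conclusion.** The point holds as a gap in commitment. The primary contrast is worded as exposed versus baseline, and adjustment for time is only to be assessed, so a time-free before-after estimate could be reported as the primary result without departing from the text. Were that done, an assumed rise of about 3.5 points per year would mimic the whole 5-point planning difference. With a linear months term the remaining exposure is to abrupt changes: about -1.2 to +2.2 points for an assumed 5-point shift at the months tried. With categorical periods a trend common to all clusters causes no bias.

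These sizes rest on the assumed start months, an assumed 326 people per cluster-month and assumed trends; the documents give no trend figure. The documents do not show that the primary analysis will ignore time, only that they do not rule it out.

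**What to change.** 1. In Data analysis, state that the primary mixed model always contains calendar period as categorical fixed effects (for example 3-month steps) together with the exposure term. Keep the language of assessing adjustment for patient and clinic covariates only. Call the contrast without time descriptive.
2. In Outcomes, reword the definition that now reads "during the intervention period (exposed) compared to baseline (unexposed") so that it refers to the period-adjusted exposure effect.
3. In Outcomes and in the segmented analysis, replace the flat 12 months of baseline with all unexposed months of each wave, in line with the trial design, baseline data collection and Exposure definition sections.
4. Report the planned time-to-exposure analysis beside the primary estimate, because a constant-effect model with period effects can understate an effect that grows. Making an exposure-time-averaged effect mandatory is optional and not part of the required change; in a quarterly model its SE was 0.0178 against 0.0110 for the constant effect, about 1.6 times larger.

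**Cost.** No new data. The SE is larger than in the time-free model: about 1.6 times in the 5-period design and about 2.4 times on the monthly timeline (1.10/0.46). Power for 5 points at 978 per cluster-period and ICC 0.01 is about 97.7% against the stated 99%.
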